### **12.2 Sample Size Determination**

*Sample Size.* We derived the sample size that is needed to detect an overall difference which is of clinical significance and with potential cost-saving implications. We have powered our study to detect the primary outcome (10% relative reduction in overall hospital admissions and overall ED visits) at 12 months. We estimate 1,500 BACO members are eligible intermediate risk patients. We know from existing institutional data that these intermediate risk BACO members experience an average of 4.3 inpatient admission over 12 months, and 10.2 ED visits over 12 months. With these baseline data, we estimate that a total sample size of 364 patients (N=182 in each arm) is adequate to detect a 10% reduction in total ED plus hospital visits with statistical power of 0.90 and two-sided type I error rate of 0.05, accounting for 80% retention over a 12-month study period.

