### **12.3 Statistical Methods**

*Study consort diagram.*

*Data Analysis Plan.* Our primary outcome is the percentage change in all-cause hospital admissions and all-cause emergency department visits (a composite outcome) in the 12 months following enrollment. Secondary outcomes include total number of all-cause ED visits; all-cause 30-day ED revisits rate; total number of all-cause discharges from IP; all-cause 30-day IP readmission rate. Intermediate measures will be measured by: number and proportion of patients to have identified HRSN; number and proportion of patients to receive referrals for their HRSN; number and proportion of patients to receive community-based services to meet their HRSN; connection to housing resources; connection to employment resources; connection to food; and patient-level average of Proportion of Days Covered (PDC) for pharmaceutical prescriptions.

We will also collect data on demographics (age, gender, race, ethnicity, and language), insurance coverage (proportion of days covered from claims data), and on potential confounding variables, such as medical comorbidity as measured by the Elixhauser score), mental health and substance use diagnoses, THRIVE screening results, and medication adherence over 12 months using a measure of proportion of days covered based on pharmacy claims data.

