| Duration of follow-up | 12 months                                                                                                                                                                                                                                                                                                                                                                                                                                                                                                                                                                                                                                                                                                                                                                                                                                                                                                                                                                                                                                                                                                     |
| Criteria for efficacy | 
Measures:
We collect data on demographics (age, gender, race, ethnicity, and language), insurance coverage (proportion of days covered from claims data), and on potential confounding variables, such as medical comorbidity as measured by a validated comorbidity index (the Charlson Comorbidity Score), mental health and substance use diagnoses, health-related social needs screening results, and medication adherence using a measure of proportion of days covered based on pharmacy claims data.
 
Primary end points:
Our primary outcome is the percentage change in all-cause hospital admissions and all-cause emergency department visits (a composite outcome) in the 12 months following enrollment.
 
Secondary end points:
Secondary outcomes include all-cause hospital admissions and all-cause emergency department visits as separate outcomes, all-cause 30-day hospital readmissions, 30-day ED revisit rates, and connection to resources (referral to food pantry, visits to food pantry, utility shutoff protection letters).
 |

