|  | 
categorical variables. Due to a potential high number of patients with zero-count visits (136 out of 364, 37%), we employ a zero-inflated negative binomial model, which is a two-part model that examines simultaneously the odds of any visit, and the rates of visits among those patients who have any health care utilization. We use Bayesian Information Criteria as the model goodness-of-fit measure to compare zero-inflated negative binomial model with other models for the rates outcomes, including over-dispersed Poisson model, and negative binomial model. As a sensitivity analysis, we also model only the binary outcome of any utilization using logit link function. In the adjusted regression models, we will control for any factors including baseline utilization that are found statistically significant between the two arms. We report odds ratios and 95% CI for binary outcome (e.g., any visit) and rate ratios for the outcomes of inpatient and ED visits. We also compare the secondary outcomes of health-related social needs (e.g., connected to community-based partner; received services through referral to community partner; referrals and visits to hospital food pantry; received utility shutoff protection letter) between the two arms and examine adjusted intervention effect using logistic regression with odds ratio and 95% CI.
 
The primary analyses will be based on intent-to-treat. Because participants may receive varying “doses” of the intervention, we will also analyze the intervention effect according to whether participants received a minimum dose of the intervention. If the pharmacy liaison-patient navigator documents in their first telephone assessment that the patient has received the THRIVE screening in the past three months, and rescreens the patient if they have not been screened in the past three months, we consider the patient to have received the minimum intervention dose.
 |

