|--|---------------------------------------------------------------------------------------------------------------------------------------------------------------------------------------------------------------------------------------------------------------------------------------------------------------------------------------------------------------------------------------------------------------------------------------------------------------------------------------------------------------------------------------------------------------------------------------------------------------------------------------------------------------------------------------------------------------------------------------------------------------------------------------------------------------------------------------------------------------------------------------------------------------------------------------------------------------------------------------------------------------------------------------------------------------------------------------------------------------------------------------------------------------------------------------------------------------------------------------------------------------------------------------------------------------------------------------------------------------------------------------------------------------------------------------------------------------------------------------------------------------------------------------------------------------------------------------------------------------------------------------------------------------------------------------------------------------------------------------------------------------------------------------------------------------------------------------------------------------------------------------------------------------------------------------------------------------------------------------------------|

- 11
- 12 **2. Major amendments to the protocol**
- 13 None
- 14
- 15 **3. Analysis population**
- 16 **3.1 Flow diagram**

Please see manuscript Figure.

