### **4.2 Participants' characteristics at inclusion**

Table 1 shows descriptive characteristics for the usual care and enhanced usual care groups. The usual care and enhanced usual care groups differed in the respective proportion who spoke English (78% vs. 87%), reported housing insecurity (9% vs. 13%), received a referral to the hospital food pantry in the past 12 months (14% vs. 25%), had at least one visit to hospital food pantry in past 12 months (12% vs. 20%) and had a diagnosis of PTSD (21% vs. 14%). The majority belonged to a racial/ethnic minority group, and 96% had received screening for health-related social needs in the past year. Approximately two-thirds of patients had significant medical comorbidity, and nearly half carried a diagnosis of depression.

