### **5.3.2 Presentation of results**

We examine descriptive statistics of all variables. For categorical variables, we will report proportions, and for continuous variables, we will report means, standard deviations, and ranges. We will assess the randomness of treatment assignment according to odd versus even patient medical record number by comparing patient characteristics by treatment status. In order to determine if the enhanced usual care intervention achieves a greater reduction (or smaller increase) in all-cause hospital admissions and all-cause emergency department visits (our composite primary outcome), respectively, in the 12 months following enrollment compared to the usual care condition, we report and compare groups on their average number of visits in the 12 months post-enrollment controlling for potential baseline differences and any covariates (e.g., age, gender) determined *a priori* as important predictors of healthcare utilization. We will note differences that are statistically significant at the  $\alpha < 0.05$  level. In the adjusted regression models, we control for any factors including baseline utilization that are found statistically significant between the two arms.

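### The protocol and the SAP name different comorbidity indices, and neither settles whether comorbidity is in the adjusted primary model

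*Combined protocol and SAP*

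**What the plan says.** Two near-identical lists of variables to be collected name different indices.

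- Protocol 12.3, among potential confounders: "medical comorbidity as measured by the Elixhauser score".
- SAP synopsis, Criteria for efficacy, Measures, also among potential confounders: "medical comorbidity as measured by a validated comorbidity index (the Charlson Comorbidity Score".

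The SAP does not explain the difference. Its section 2, headed "Major amendments to the protocol", has the single entry None.

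Neither document names comorbidity as a term in the primary model. Two rules could bring it in.

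- SAP synopsis (Statistical method), repeated in substance in SAP 5.1 and 5.3.2: "we will control for any factors including baseline utilization that are found statistically significant between the two arms".
- Protocol 12.3 and SAP 5.3.2: adjustment for "any covariates (e.g., age, gender) determined *a priori* as important predictors of healthcare utilization". Neither document completes this list.

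The SAP text also contains results. SAP 4.2 reports "Approximately two-thirds of patients had significant medical comorbidity", and names the characteristics on which the arms differed: English language, housing insecurity, food pantry referral, food pantry visits and PTSD. The Statistical method entry supports the zero-inflated model with a count: "Due to a potential high number of patients with zero-count visits (136 out of 364, 37" per cent).

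**The concern.** The two documents cannot both be followed on the comorbidity index, and a reader cannot tell which one governs. The index also affects the analysis. Under the significance rule it decides whether comorbidity is adjusted for at all. Under the a priori rule it decides which variable is used.

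Adjustment matters more here than in a trial with concealed randomisation. Arms are set by odd or even record number, each arm's own liaisons approach its patients, and patients enter only if they agree (protocol 9, Assignment to Study Arm Procedures; SAP synopsis, Randomization and treatment procedures). The SAP already reports some baseline differences. If the choice of index and the decision to adjust are both unsettled in a text that holds baseline and outcome counts, the adjusted estimate cannot be shown to have been fixed in advance on this point.

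**Working it through.** **1. Does any stated figure depend on the index?** Protocol 12.2 gives 4.3 admissions and 10.2 ED visits per 12 months, a 10% relative reduction, and "statistical power of 0.90 and two-sided type I error rate of 0.05, accounting for 80% retention over a 12-month study period". No standard deviation is given, so I assume Poisson variance, equal in both arms.

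- Mean = 4.3 + 10.2 = 14.5; difference = 0.10 × 14.5 = 1.45; variance = 14.5 (SD 3.81).
- n per arm = 2 × (1.960 + 1.282)² × 14.5 / 1.45² = 144.9, rounded up to 145.
- Retention: 145 / 0.80 = 181.25, rounded up to 182 per arm, 364 in total.

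This matches the stated figure. No covariate enters the calculation, so the choice of index does not change it.

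**2. Would the SAP's significance rule bring comorbidity in?** SAP 4.2 does not list it as differing. That list seems, if anything, wider than the rule. Housing insecurity is on it at 9% v 13%. With an assumed 182 per arm, z = 0.04 / √(0.11 × 0.89 × 2/182) = 0.04 / 0.0328 = 1.22, below 1.96. Comorbidity is absent even from this list, so on the reported results the rule would probably leave it out. Its only other way in is the incomplete a priori list.

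**3. How often would two indices give different answers under that rule?** Treat the two baseline z-statistics as bivariate normal with correlation ρ (assumed; 2,000,000 draws), each tested at two-sided 0.05. The chance that exactly one is significant is 2 × P(either) − 0.10.

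| ρ | P(either significant) | P(exactly one significant) |
|---|---|---|
| 0.5 | 0.091 | 0.08 |
| 0.7 | 0.083 | 0.07 |
| 0.9 | 0.071 | 0.04 |

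For one fixed index the first figure is 0.05. These are rates of chance baseline imbalance, not error rates for the treatment effect.

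**4. What could free choice do to the treatment comparison?** Assume no treatment effect, 182 per arm, a linear model, correlation ρ between the indices, and the same correlation r of each index with the outcome. In 20,000 simulated trials per row, the analyst either fixes one index or reports the more favourable of the two.

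| ρ | r | Type I error, index fixed | Type I error, better of two |
|---|---|---|---|
| 0.5 | 0.2 | 0.051 | 0.061 |
| 0.5 | 0.4 | 0.050 | 0.071 |
| 0.7 | 0.2 | 0.051 | 0.059 |
| 0.7 | 0.4 | 0.050 | 0.065 |
| 0.9 | 0.2 | 0.048 | 0.053 |
| 0.9 | 0.4 | 0.049 | 0.058 |

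The simulation standard error near 0.05 is √(0.05 × 0.95 / 20,000) = 0.0015. This is a ceiling on the effect of choosing between indices, because it supposes deliberate selection. It is not computed under the SAP's zero-inflated negative binomial model.

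**5. Can the order of events be established?** SAP 3.2 puts recruitment at May 2019 to March 2020, so 12-month follow-up would end by March 2021. Protocol version 1.3 is dated August 5, 2021 and still names Elixhauser. The SAP text I worked from carries no date (its title page was not included). The SAP text as it stands was therefore written with data in hand, but the date on which the index changed is unknown.

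**The case against.** The other side has a good deal to say. The SAP is the more specific analysis document and names exactly one index, so nobody is invited to try both. Comorbidity is only a listed potential confounder; the one factor singled out for the adjusted models is baseline utilization. Replacing one comorbidity index with another in such a list is not plainly a major amendment. SAP 4.2 gives one pooled statement about comorbidity, with no index named and no figures by arm. Adding a covariate now would itself be a decision made after data were seen. And the larger freedom lies in the covariate rule, not in the name of the index.

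Most of this stands, and it rules out several stronger readings that a reader might infer:

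- That a primary-model covariate was switched. Neither document puts comorbidity in that model by name.
- That Charlson was chosen because of what Elixhauser showed. The SAP summarises comorbidity without saying which index it used, and nothing dates the change.
- That the entry of None in SAP section 2 is false. It covers only major amendments.

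What the objection does not remove is the unexplained mismatch, or the fact that whether comorbidity is adjusted for at all is still undecided in a text that holds results. A covariate added late is a cost, but the SAP reports comorbidity and the zero count only in pooled form. A dated, disclosed rule that ignores the baseline p-value leaves less room for choice than the present one.

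**Conclusion.** The point holds as a minor inconsistency with a real but small consequence. The documents disagree on the index, give no reason, and leave open both which index is used and whether comorbidity is adjusted for.

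Under the stated assumptions (correlation between indices 0.5-0.9, correlation of each with the outcome 0.2-0.4, linear model), the most that free choice of index could do is raise the two-sided type I error from 0.05 to about 0.053-0.071. A reader might take the 7-9% chance that at least one index is imbalanced as an error rate for the treatment effect; it is not. Nor do the documents support a finding that the analysis was steered by results. The sample size is unaffected. Separately from the index, leaving out a prognostic baseline measure because it happens not to differ significantly between arms is a poor reason, and it is the part most worth correcting.

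**What to change.** - Reconcile protocol 12.3 and the SAP synopsis to one comorbidity index. Either is defensible; the documents give no ground for preferring one.
- Compute it from diagnoses dated before enrolment. State the look-back window and the form used (score or categories).
- Enter it as a fixed covariate in the adjusted primary model regardless of baseline significance, and say whether it enters both parts of the zero-inflated model.
- Report the other index as a sensitivity analysis.
- Record in the SAP the date of and reason for the change, and say that the covariate was fixed after the pooled counts now in the text were known.

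The cost is a few sentences across the two documents, one model term and one extra model run. Diagnoses should be available from the claims data and clinical data warehouse already in use, so no new data collection is expected, and the sample size stays at 364.

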#### 4.2.2 Secondary Outcome Measures

Secondary outcomes measures will be measured by:

1. Total number of all-cause ED visits;
2. Total number of all-cause 30-day ED revisits;
3. All-cause 30-day ED revisits rate;
4. Total number of all-cause discharges from IP;
5. Total number of all-cause 30-day IP readmissions;
6. All-cause 30-day IP readmission rate.

Intermediate measures will be measured by:

1. Number and proportion of patients to have identified HRSN;
2. Number and proportion of patients to receive referrals for their HRSN;
3. Number and proportion of patients to receive community-based services to meet their HRSN;
4. Connection to housing resources;
5. Connection to employment resources;
6. Connection to food;
7. Patient-level average of Proportion of Days Covered (PDC) for pharmaceutical prescriptions.

A budget impact analysis will be conducted to estimate the short-term expenditure changes and financial consequences of THRIVE+ compared to THRIVE-Basic, focusing on direct costs of implementation (staffing, resources, eligible intervention population size, etc.).

Post-hoc measures:

1. Social determinants of health services or referrals (e.g., food pantry referrals, food pantry visits, utilities shut-off protection letters).

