| Patients to receive services to meet their HRSN     | Action for Boston Community Development data                                                                                                       | Research     | Quarterly – All enrolled patients                                                                                                                                                      |
| Connection to housing resources                     | Action for Boston Community Development data                                                                                                       | Research     | Quarterly – All enrolled patients                                                                                                                                                      |
| Connection to employment resources                  | Action for Boston Community Development data                                                                                                       | Research     | Quarterly – All enrolled patients                                                                                                                                                      |
| Connection to food                                  | Action for Boston Community Development data                                                                                                       | Research     | Quarterly – All enrolled patients                                                                                                                                                      |
| Patient-level average of Proportion of Days Covered | BMC HealthNet Plan claims data                                                                                                                     | Routine Care | Quarterly – All enrolled patients                                                                                                                                                      |

|                                        |  |  |  |
|----------------------------------------|--|--|--|
| (PDC) for pharmaceutical prescriptions |  |  |  |
|----------------------------------------|--|--|--|

Table 2. Post-Hoc Measures

| Post-hoc measure                                     | Data Source                 | Data collected as part of Routine Care or for Research? | Measurement Time Points (Post-Enrollment) |

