|------------------------------------------------------|-----------------------------|---------------------------------------------------------|-------------------------------------------|
| PRIMARY OUTCOME                                      |                             |                                                         |                                           |
| Social determinants of health referrals and services | BMC Clinical Data Warehouse | Routine Care                                            | 12 Months – all study participants        |

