## **6. Secondary efficacy outcomes analysis**

## **6.1 Definitions**

Secondary outcomes include all-cause hospital admissions and all-cause emergency department visits as separate outcomes, all-cause 30-day hospital readmissions, 30-day ED revisit rates, and connection to resources (visits to food pantry, receipt of utility shutoff protection letter).

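### The SAP presents three measures that the protocol calls post hoc (pantry referral, pantry visits, utility letters) as secondary outcomes, and adjusts for their prior values only if these test significant

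*Combined protocol and SAP*

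**What the plan says.** **Protocol.** Section 4.2.2 gives six secondary and seven intermediate measures. It then gives a separate post-hoc list with one entry: "Social determinants of health services or referrals (e.g., food pantry referrals, food pantry visits, utilities shut-off protection letters". Section 9 repeats the separation in "Table 2. Post-Hoc Measures", whose single row is "Social determinants of health referrals and services", taken from the Clinical Data Warehouse at 12 months for all participants. The analysis plan in section 12.3 does not mention these measures.

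**SAP.** Three places treat them as secondary outcomes:
- The synopsis, under secondary end points: "connection to resources (referral to food pantry, visits to food pantry, utility shutoff protection letters".
- The synopsis, under statistical method, for logistic regression with odds ratios and 95% confidence intervals: "referrals and visits to hospital food pantry; received utility shutoff protection letter".
- Section 6.1: "connection to resources (visits to food pantry, receipt of utility shutoff protection letter". Pantry referral is missing here.

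None of the three uses the term post hoc. Section 2, headed "Major amendments to the protocol", has the entry None.

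**Adjustment.** The SAP synopsis and sections 5.1 and 5.3.2 control for factors, including baseline utilization, that are found statistically significant between the arms. Section 6.2 carries similar methods, both bivariate and adjusted, to the secondary outcomes.

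**Data already seen.** The SAP quotes 136 of 364 patients with no visits, gives recruitment dates in the past tense (May 2019 through March 2020), and reports characteristics at inclusion by arm. These include pantry referral and pantry visits over the past 12 months.

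**The concern.** A reader who has only the SAP would take all its secondary outcomes as planned before the data were seen. For these three measures the protocol says otherwise, and the SAP does not disclose the change. If a pantry or utility-letter comparison came out in favor of THRIVE+, it would be read as confirmation of a planned outcome when it should be read as exploratory.

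The label matters more here because two of the three measures favored the intervention arm before any intervention was given. An analysis that does not allow for this could show a difference that was there at the start. Whether the SAP allows for it depends on a significance test at baseline.

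**Working it through.** **1. Status of each measure, side by side**

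| Measure | Protocol 4.2.2 and Table 2 | SAP synopsis, end points | SAP synopsis, method | SAP 6.1 |
|---|---|---|---|---|
| Pantry referral | post hoc | secondary | secondary | not listed |
| Pantry visits | post hoc | secondary | secondary | secondary |
| Utility letter | post hoc | secondary | secondary | secondary |

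The nearest planned measure is "Connection to food", an intermediate outcome. Table 1 draws it from the community partner's data. It does not cover the hospital pantry or utility letters.

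**2. Timing.** The SAP's count reproduces: 136/364 = 0.374, stated as 37%. Recruitment ended in March 2020, so 12-month follow-up ended by about March 2021. The current protocol, which still says post hoc, is version 1.3 of August 5, 2021.

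**3. Imbalance at inclusion (SAP 4.2)**
- Referral, 14% vs 25%: odds ratio (0.25/0.75)/(0.14/0.86) = 2.05.
- Visits, 12% vs 20%: odds ratio (0.20/0.80)/(0.12/0.88) = 1.83.
- Utility letters: the SAP text gives no prior-period figure.

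**4. Would the adjustment rule include these factors?** The SAP text gives neither counts nor arm sizes, so I assume 182 per arm and round the percentages to counts.
- Referral, 25/182 vs 46/182: chi-square p = 0.005, or 0.008 with continuity correction. Adjusted for either way.
- Visits, 22/182 vs 36/182: chi-square = 364 × (22×146 − 36×160)² / (182×182×58×306) = 4.02, p = 0.045. With continuity correction, 364 × (2548 − 182)² / (182×182×58×306) = 3.47, p = 0.063.

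The visits result is sensitive to rounding. At 182 per arm, 12% can be 21 or 22 patients and 20% can be 36 or 37. Over these four combinations the uncorrected p runs from 0.022 to 0.045 and the corrected p from 0.032 to 0.063. Only 22 vs 36 straddles 0.05. The SAP names chi-square tests but does not say whether the correction applies.

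Section 4.2 names visits among the characteristics that differed, but this does not settle the matter. The same list includes housing insecurity, 9% vs 13%. At 182 per arm (16 or 17 vs 23 or 24) that gives an uncorrected p between 0.18 and 0.31. The word there does not track statistical significance.

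**5. What an unadjusted comparison could show.** Suppose the inclusion percentages were the true rates and simply persisted, with no intervention effect. The chance of a two-sided p below 0.05 is Φ{(|p2 − p1| − 1.96√[2p̄(1−p̄)/n]) / √[(p1(1−p1) + p2(1−p2))/n]} with n = 182:
- Referral: (0.110 − 0.0814)/0.0411 = 0.695, chance about 76%.
- Visits: (0.080 − 0.0753)/0.0382 = 0.122, chance about 55%.

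These are upper illustrations. If the imbalance was partly chance, the rates would drift together and the figures would fall.

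**The case against.** The strongest reply is that this is a labelling difference in non-primary outcomes and that the SAP already handles the imbalance. It plans adjusted logistic regression with confidence intervals for these measures, and it adjusts for factors that differ significantly. On the figures above, prior referral would enter the model. This much stands: the inclusion odds ratio of about 2 would not pass straight into the adjusted referral result. It does not secure adjustment for prior visits. The SAP gives no prior-period figure for letters, and section 6.2 also plans a bivariate comparison.

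It can also be said that SAP section 2 concerns amendments to the protocol, and the protocol still says post hoc. On that view the SAP departs from the protocol without there being an undeclared amendment. That is fair, but the departure is then recorded nowhere.

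Several stronger readings are tempting and are not supported:
- **Selection on results.** The SAP quotes a visit count not split by arm, recruitment dates and inclusion characteristics. It gives no 12-month result by arm for any of the three measures.
- **Planned mechanism outcomes untested.** The SAP synopsis keeps connection to, and services through, the community partner. What its outcome lists lack by name is narrower: connection to housing, connection to employment, and PDC, which remains only as a covariate. Those lists are also worded as open.
- **30-day measures removed.** The SAP lists 30-day readmissions. Protocol 12.3 itself omits both 30-day totals, so their absence is not a change made by the SAP.
- **SAP 5.2.** Its None falls under the primary outcome and says nothing about these measures.
- **Multiplicity.** Three tests at 0.05 give 1 − 0.95³ = 14.3%, and the two in section 6.1 give 1 − 0.95² = 9.75%, if independent. Referral and visits are probably correlated, and the lack of multiplicity control affects every secondary outcome. The point does not rest on this.

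**Conclusion.** The point holds as a matter of text: measures that the protocol labels post hoc appear in the SAP as secondary outcomes, without disclosure, in a document written with data in hand. A reader might infer that they were picked because they looked favorable. The documents neither show this nor exclude it.

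The imbalance makes the label consequential. Referral and visits favored the intervention arm at inclusion with odds ratios of about 2.05 and 1.8. Adjustment for prior visits is not assured: under one of the four count pairs compatible with the rounded percentages, it depends on whether a continuity correction is used. That result assumes 182 per arm. Neither the primary outcome nor its analysis is affected.

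**What to change.** 1. In the SAP synopsis (secondary end points and statistical method) and in section 6.1, list the same three measures and label them post hoc and exploratory. Report estimates with confidence intervals and make no claim of significance.
2. Adjust each for the same measure in the prior 12 months wherever it is available, whatever the baseline test shows.
3. State in the SAP how it departs from the protocol. Include that connection to housing, connection to employment and PDC, all planned intermediate outcomes, are absent from its outcome lists. Report those outcomes as planned.

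The cost is SAP wording, a weaker label for three outcomes and one added covariate per model.
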